Study Title: Effectiveness of a pressure-sensing mattress system for reducing the risk of pressure ulcer formation by lowering interface pressure in vulnerable patient populations: Parallel-two-group randomized trial

PI: [name]

Version number/date: V2 01/04/2014

component of prevention and treatment protocols. The best practices pertaining to a specific turning regiment varies from the National Pressure Ulcer Advisory Panel (NPUAP) recommending repositioning every two hours and the European Pressure Ulcer Advisory Panel (EPUAP) recommending every four hours. Thus pressure ulcer prevention and management are necessarily labour-intensive.

Continuous pressure imaging (or interface pressure mapping) of the interface pressure between the body and support surface could be an effective technology as part of an overall strategy for the prevention and management of ulcers. By placing a thin mattress or sensor pad with monitoring capabilities under a patient, pressure imaging interprets the interface pressures and provides the patient's real-time pressure points on a corresponding computer screen, which can assist healthcare providers determine when a patient should be re-positioned (Hanson). XSENSOR Technology Corporation designed the ForeSite PT™ Patient Turn System (here in "ForeSite PT™ system"), which can continuously monitor bed surface interface pressure and track the patient's exposure to that pressure. The ForeSite PT™ system provides patient turn tracking to assist with management of the patient turn schedule. The pressure exposure monitor provides a visual image that quantifies historical pressure information. The exposure monitor assists clinical staff by alerting them to the location of body areas that have experienced the greatest exposure to pressure. The surface pressure monitor provides clinical staff with a visual image of the pressure distribution across a patient's body. It can be used by care providers to identify high pressure areas in real time and to validate that patient repositioning has successfully relieved pressure.

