## **Methods**

### **Trial design**

A parallel two group randomized controlled clinical trial will be conducted to assess the use of ForeSite PT™ system on a pressure-related skin and tissue changes, with progression to pressure ulceration; interface pressure; and the perceptions of healthcare providers and patients to the ForeSite PT™ system. Eligible consenting inpatients will be randomly allocated to either have the ForeSite PT™ system and the LCD monitor turned on (intervention group), or have the ForeSite PT™ system and the LCD monitor turned off (control group) in a ratio of 1:1. Both groups will be included in the study up to a maximum of 7 days. Interface pressure and clinical outcomes will be measured at baseline (within 24 hours of admission) and on the last day of enrollment in the trial (within 24 hours prior to discharge, or on the seventh day (whichever comes first)). The perceptions of patients allocated to the intervention group, and the perceptions of healthcare providers each time a patient in their care is allocated to the intervention group, will be measured on the last day of enrollment in the trial or on the seventh day (whichever comes first).

Ethics ID number: REB13-0794

Study Title: Effectiveness of a pressure-sensing mattress system for reducing the risk of pressure ulcer formation by lowering interface pressure in vulnerable patient populations: Parallel-two-group randomized trial

PI: [name]

Version number/date: V2 01/04/2014

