## 185 **Control Group**

186 Inpatients allocated to the control group will have the ForeSite PT™ system's LCD monitor turned off and  
187 hidden (i.e., real-time images of interface pressure will not be displayed on the monitor). As the ForeSite  
188 PT™ system will continue to sample interface pressure with the display turned off, this enables patients  
189 enrolled in the control group to undergo silent monitoring.

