## 190 **Outcomes**

### 191 **Primary Outcome**

- 192 1. A composite of interface pressure measurements that reflect the distribution of interface pressure  
193 at predetermined time intervals. These measures include:
- 194 a. proportion of participants that have pressure readings greater than 40 mmHg;
  - 195 b. average interface pressure (excluding sensels with 0mmHg reading); and
  - 196 c. the absolute number of sensels with pressure readings greater than 40 mmHg.

197 The measurement of this outcome will be facilitated by the ForeSite PT™ system's sensor overlay that  
198 continuously collects pressure readings. The array of the sensor overlay is a capacitive sensor with a  
199 0.625" spatial resolution. There are 52 rows x 118 columns for 6,136 sensing points. The ForeSite PT™  
200 system's software continuously samples interface pressure at a rate of 1 Hz, which can then be  
201 extracted for analysis. The data file is in a proprietary binary format, and can be exported to TXT or CSV  
202 formats for import into a spreadsheet program for analysis. This will be achieved by the sampling of  
203 pressure readings at specified time intervals before and after turning/repositioning when the ForeSite  
204 PT™ system's LCD monitor is turned on, and when it is turned off.

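### The primary pressure readings are anchored to turns, whose timing and number the display is meant to influence, so they need not reflect pressure over time

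*Protocol*

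**What the plan says.** Three statements in the protocol bear on when the primary outcome is measured.

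- **Primary Outcome, definition.** The outcome is "A composite of interface pressure measurements that reflect the distribution of interface pressure", taken "at predetermined time intervals. These measures include" (three components follow): (a) the share of participants with readings above 40 mmHg, (b) the mean pressure over sensels that do not read zero, and (c) the count of sensels above 40 mmHg. Turns are not mentioned here.
- **Primary Outcome, measurement.** The end of the same section says the outcome will be obtained by sampling "pressure readings at specified time intervals before and after turning/repositioning when the ForeSite" display is on, and when it is off.
- **Trial design.** "Interface pressure and clinical outcomes will be measured at baseline (within 24 hours of admission) and on the last day of enrollment in the trial".

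On the data available, the Primary Outcome section says the "system's software continuously samples interface pressure at a rate of 1 Hz, which can then be" extracted. The Control Group section says that recording with the display off allows patients "enrolled in the control group to undergo silent monitoring". A continuous record therefore exists in both arms.

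On the link between display and turning, the Background says that pressure imaging gives a real-time picture "which can assist healthcare providers determine when a patient should be re-positioned". It adds that the system tracks turns to help manage the turn schedule, and that staff can use the pressure map "to validate that patient repositioning has successfully relieved pressure". Research question 1 in the Objectives asks whether the system lowers pressure by helping staff choose how to turn the patient.

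**The concern.** A randomised comparison needs both arms to be measured by a rule that treatment cannot affect. Here the reference point for measurement is the turn, which occurs after randomisation and is the behaviour that the display is meant to influence. Three consequences follow.

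1. **Duration drops out.** The Background names prolonged pressure as a primary cause of ulcers and says the monitor's risk information depends on how long pressure has lasted at a site. None of the three components carries duration. If the display leads staff to end a bad position sooner, readings taken just before and just after turns need not change.
2. **The moments may be selected differently by arm.** After a turn, staff in the display arm can check the map and adjust; staff in the control arm cannot. A reading soon after the turn could catch a short-lived improvement.
3. **The number of readings can differ by arm.** If component a counts a participant who has any sampled reading above 40 mmHg, an arm that is turned more often has more chances of an event.

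At stake is whether the primary comparison answers the primary objective, which is reduced interface pressure.

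**Working it through.** **The plan's own figure.** The Sample size section gives 294 per arm for 30% against 20%, alpha 0.05 and 80% power. With a pooled variance, two-sided and without continuity correction:

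n = [1.960 × √(2 × 0.25 × 0.75) + 0.842 × √(0.30 × 0.70 + 0.20 × 0.80)]² / 0.10², rounded up = 294.

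This reproduces the stated figure. Power at the planned 300 per arm is 80.9%. The arithmetic is not in dispute.

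The protocol gives no turn rates, hold times, pressures or reading weights. Every input in checks 1 to 3 is therefore an assumption, apart from the 30%, 20% and 300 per arm. The hold times are for illustration only and imply nothing about care.

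**Check 1: a real fall that is missed.** Assume half of positions have 100 sensels above 40 mmHg and half have 200. Control patients hold each for 2 h. The display arm ends the 200-sensel positions early. Turn-anchored readings are weighted equally.

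| | Turn-anchored mean | Time-weighted mean |
|---|---|---|
| Control, 2 h and 2 h | (100 + 200)/2 = 150 | (100×2 + 200×2)/4 = 150 |
| Display, bad position ended at 60 min | 150 | (100×2 + 200×1)/3 = 133 (-11%) |
| Display, bad position ended at 30 min | 150 | (100×2 + 200×0.5)/2.5 = 120 (-20%) |

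The same holds for mean pressure. With positions alternating between 45 and 25 mmHg and 2-h holds in control, shortening the 45 mmHg hold to 1.5, 1 or 0.5 h leaves the turn-anchored mean at 35.0 mmHg. The time-weighted mean falls to 33.6, 31.7 or 29.0 mmHg.

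**Check 2: a brief fall that is exaggerated.** Assume 150 sensels throughout in control. In the display arm the count is 120 for the first 10 min of a 2-h position and 150 for the remaining 110 min.

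- Turn-anchored: (150 before + 120 after)/2 = 135, or -10%.
- Time-weighted: (120×10 + 150×110)/120 = 147.5, or -1.7%.

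In mmHg, take 40 before the turn and 25 for 5, 15 or 30 min of a 120-min cycle, then 40 again. The turn-anchored mean is 32.5, a fall of 7.5. The time-weighted mean is 39.4, 38.1 or 36.3, a fall of only 0.6 to 3.8.

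**Check 3: component a read as any sampled reading above 40 mmHg.** Assume independent readings, and that 30% against 20% holds when both arms have equal numbers of turns. If the display arm is turned r times as often, its event rate is 1 - 0.80^r.

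| r | Display-arm rate | Power at 300 per arm against 30% |
|---|---|---|
| 1 | 20.0% | 81% |
| 1.25 | 24.3% | 34% |
| 1.5 | 28.4% | 6% |
| 2 | 36.0% | direction reverses |

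Readings within a patient are correlated, so these are the outer end of the range. If a patient's readings were all alike, the rate would stay at 20% whatever r is.

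**Timing statements side by side.** Fixed intervals, intervals around turns, and two occasions (baseline and last day) are three different sampling schemes. A turn is not a predetermined time, and the protocol does not say whether turn-anchored sampling is confined to the first and last days or runs throughout.

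**The case against.** Several points on the other side are fair.

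- **The display does not dictate turns.** A reader might infer that the display triggers the turns at which readings are taken. The Background says only that it assists the decision, and the Intervention section gives usual care to both arms. What stands is that the display can alter timing and number.
- **Equal weighting is not stated.** It follows if a fixed number of readings is taken per turn, which is the natural reading. The protocol gives neither the intervals nor the weights, and an analysis plan may do so. That plan would still inherit the turn as anchor, because the protocol states it as the rule.
- **Selection of bad moments is possible, not documented.** A reader might infer that display-arm readings before a turn are chosen because the map looked bad, and that those after it show the best moment. Readings are extracted from a continuous record, and the delay after the turn is not given.
- **Participants without any turn should be rare.** Eligibility requires a need for help with bed mobility and excludes those whom turning would harm.
- **Before-and-after readings suit research question 1**, which concerns the method of turning. That is a reason to keep them. The primary objective, however, is lower pressure, and turn quality is the route to it.
- **The examples build in their result.** Checks 1 and 2 each isolate one mechanism. They show that the error can occur in either direction, not how large it will be. They also concern continuous measures, whereas the trial is sized on a binary event and the analysis section names Chi-square or Fisher tests for the primary outcome. A power figure for a comparison of means would not describe the planned test.

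**Conclusion.** The point holds in a limited form. The protocol ties its primary readings to a post-randomisation event that the intervention is intended to influence. Unless time weighting is added, those readings do not represent exposure. The sampling rule also conflicts with the two other timing statements.

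The size cannot be estimated from the document. Under the assumed values, a true reduction of 11% to 20% can show as zero, and a true reduction of 1.7% can show as 10%. Under the any-reading interpretation of component a with independent readings, 1.5 times as many turns would cut power from 81% to 6%.

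A reader might go further and infer that the direction of any bias could never be known. The document does not support that: the 1 Hz files exist in both arms, so time-weighted values can be computed and compared with turn-anchored ones later. No data are lost. What would be lost is prespecification, which is why the rule should be settled before analysis. The sample size of 294 is unaffected arithmetically, but the event rates behind it depend on how component a is defined.

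**What to change.** 1. **Reconcile the timing.** Make the two statements in the Primary Outcome section and the one in Trial design describe a single sampling scheme.
2. **Remove the turn anchor.** Before analysis, define the primary measures from the existing 1 Hz record on a schedule that is independent of turns and identical in both arms. This can be a time-weighted value or readings at fixed clock times, over a common in-bed window, with one value per participant.
3. **Redefine component a** so that it does not depend on the number of readings, for example as a participant-level event based on a prespecified share of in-bed time above 40 mmHg. This is needed even with clock sampling: every 10 minutes for 7 days gives up to 7 × 24 × 6 = 1,008 frames, and an any-reading rule over that many would push the event rate up in both arms.
4. **Recheck the 30% and 20% rates** in the Sample size section against the redefined event.
5. **Keep the before-and-after-turn readings** as a secondary or descriptive measure of turn quality.

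The cost is a wording change, scripted data reduction and a rechecked event-rate assumption, which could change the required sample size. No new measurement is needed. The trade-off is that turn quality would no longer be the primary measure.

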### 205 **Secondary Outcomes**

Ethics ID number: REB13-0794

Study Title: Effectiveness of a pressure-sensing mattress system for reducing the risk of pressure ulcer formation  
by lowering interface pressure in vulnerable patient populations: Parallel-two-group randomized trial

PI: [name]

Version number/date: V2 01/04/2014

- 206 1. A composite of endpoints that reflect compromised skin and soft tissues, with potential for  
 207 progression to overt pressure ulceration. This will include:  
 208 a. skin discolouration;  
 209 b. localized tenderness without skin breakdown;  
 210 c. Stage I and II (partial thickness) pressure ulcer formation;  
 211 d. Stage III and IV (full thickness) pressure ulcer formation;  
 212 e. unstageable/Unclassified: Full thickness skin or tissue loss – depth unknown;  
 213 f. suspected Deep Tissue Injury – depth unknown; or  
 214 g. presence of any skin or wound infection (i.e., cellulitis, infected ulcers, or osteomyelitis).

215 This outcome will be measured by a head-to-toe skin clinical assessment for detection of pressure-  
 216 related skin changes and for overt ulceration by the Research Nurse. This assessment will be conducted  
 217 within 24 hours of admission and 24 hours prior to discharge, or on the seventh day (whichever comes  
 218 first). This information will be noted on a form, which requires the Research Nurse to circle the skin  
 219 areas where the patient may have skin changes or a pressure ulcer. They will label the circled area with  
 220 the numbers 1 to 9 that correspond to predetermined categories of pressure-related skin changes and  
 221 stages of pressure ulcer development.

222 The presence of a pressure ulcer and its severity, as well as the development of other skin condition  
 223 changes, will be determined as per the National Pressure Ulcer Advisory Panel's categories/staging  
 224 definitions (2,3,4,5,6,7) and other skin appearance changes (1,8,9) described below:

| Numbered Labels                                                                           | Descriptions                                                                                                                                                                                                                                                                                                                                                                                                                                                       |
|-------------------------------------------------------------------------------------------|--------------------------------------------------------------------------------------------------------------------------------------------------------------------------------------------------------------------------------------------------------------------------------------------------------------------------------------------------------------------------------------------------------------------------------------------------------------------|
| 1. Pressure-related blanchable erythema (excluding dermatitis, cellulitis, trauma) | Intact skin with redness; skin remains blanchable on compression, potentially reversible change                                                                                                                                                                                                                                                                                                                                                                    |
| 2. Stage I pressure ulcer (non-blanchable erythema)                                | Intact skin with non-blanchable redness of a localized area usually over a bony prominence. Darkly pigmented skin may not have visible blanching; its color may differ from the surrounding area. The area may be painful, firm, soft, warmer or cooler as compared to adjacent tissue. Category I may be difficult to detect in individuals with dark skin tones. May indicate "at risk" persons.                                                                 |
| 3. Stage II pressure ulcer (partial thickness skin loss)                           | Partial thickness loss of dermis presenting as a shallow open ulcer with a red pink wound bed, without slough. May also present as an intact or open/ruptured serum-filled or sero-sanguinous filled blister. Presents as a shiny or dry shallow ulcer without slough or bruising*. This category should not be used to describe skin tears, tape burns, incontinence associated dermatitis, maceration or excoriation.
*Bruising indicates deep tissue injury. |

Ethics ID number: REB13-0794

Study Title: Effectiveness of a pressure-sensing mattress system for reducing the risk of pressure ulcer formation by lowering interface pressure in vulnerable patient populations: Parallel-two-group randomized trial

PI: [name]

Version number/date: V2 01/04/2014

|                                                                                               |                                                                                                                                                                                                                                                                                                                                                                                                                                                                                                                                                                                                                                 |
|-----------------------------------------------------------------------------------------------|---------------------------------------------------------------------------------------------------------------------------------------------------------------------------------------------------------------------------------------------------------------------------------------------------------------------------------------------------------------------------------------------------------------------------------------------------------------------------------------------------------------------------------------------------------------------------------------------------------------------------------|
| 
4. Stage III pressure ulcer (full thickness skin loss)
                          | 
Full thickness tissue loss. Subcutaneous fat may be visible but bone, tendon or muscle are not exposed. Slough may be present but does not obscure the depth of tissue loss. May include undermining and tunneling. The depth of a Category/Stage III pressure ulcer varies by anatomical location. The bridge of the nose, ear, occiput and malleolus do not have (adipose) subcutaneous tissue and Category/Stage III ulcers can be shallow. In contrast, areas of significant adiposity can develop extremely deep Category/Stage III pressure ulcers. Bone/tendon is not visible or directly palpable.
 |
| 
5. Stage IV pressure ulcer (full thickness tissue loss)
                         | 
Full thickness tissue loss with exposed bone, tendon or muscle. Slough or eschar may be present. Often includes undermining and tunneling. The depth of a Category/Stage IV pressure ulcer varies by anatomical location. The bridge of the nose, ear, occiput and malleolus do not have (adipose) subcutaneous tissue and these ulcers can be shallow. Category/Stage IV ulcers can extend into muscle and/or supporting structures (e.g., fascia, tendon or joint capsule) making osteomyelitis or osteitis likely to occur. Exposed bone/muscle is visible or directly palpable.
                                      |
| 
6. Unstageable/Unclassified: Full thickness skin or tissue loss – depth unknown
 | 
Full thickness tissue loss in which actual depth of the ulcer is completely obscured by slough (yellow, tan, gray, green or brown) and/or eschar (tan, brown or black) in the wound bed. Until enough slough and/or eschar are removed to expose the base of the wound, the true depth cannot be determined; but it will be either a Category/Stage III or IV. Stable (dry, adherent, intact without erythema or fluctuance) eschar on the heels serves as “the body’s natural (biological) cover” and should not be removed.
                                                                                            |
| 
7. Suspected Deep Tissue Injury – depth unknown
                                 | 
Purple or maroon localized area of discolored intact skin or blood-filled blister due to damage of underlying soft tissue from pressure and/or shear. The area may be preceded by tissue that is painful, firm, mushy, boggy, warmer or cooler as compared to adjacent tissue. Deep tissue injury may be difficult to detect in individuals with dark skin tones. Evolution may include a thin blister over a dark wound bed. The wound may further evolve and become covered by thin eschar. Evolution may be rapid exposing additional
                                                                          |

Ethics ID number: REB13-0794

Study Title: Effectiveness of a pressure-sensing mattress system for reducing the risk of pressure ulcer formation by lowering interface pressure in vulnerable patient populations: Parallel-two-group randomized trial

PI: [name]

Version number/date: V2 01/04/2014

|                                                           |                                                                                                                                                   |
|-----------------------------------------------------------|---------------------------------------------------------------------------------------------------------------------------------------------------|
|                                                           | layers of tissue even with optimal treatment.                                                                                                     |
| 8. Infection – cellulitis around pressure ulcer    | This presents as redness, warmth and swelling in the skin around the pressure ulcers.                                                             |
| 9. Infection – pressure ulcer wound base infection | This presents as drainage (potentially purulent) with strong odour from the base of the pressure ulcer. May have necrotic material as wound base. |

225

226 2. Perceptions (both positive and negative) of healthcare providers caring for patients allocated to the  
227 treatment group to the ForeSite PT™ system. This outcome will be measured by a survey consisting  
228 of 17 close-ended and open-ended questions about prior experience with pressure mapping  
229 technology, and functionality, ease of use, and interpretation of pressure data on the LCD monitor.  
230 These questions were utilized in a prior pilot study assessing healthcare providers' perceptions to  
231 the interface pressure information provided on the LCD monitor, and the impact of this information  
232 on patient care. The survey will be administered to each healthcare provider once after their first  
233 use of the ForeSite PT™ system in the trial by the Research Nurse or the Research Assistant on the  
234 patient's last day of enrollment or on the seventh day (whichever comes first), and will take  
235 approximately 10 minutes to complete.

236

237 3. Perceptions (both positive and negative) of patients (and if appropriate, family members) allocated  
238 to the treatment group to the ForeSite PT™ system. This outcome will be measured by a survey  
239 consisting of seven close-ended and open-ended questions about prior experience with pressure  
240 mapping technology and the ForeSite PT™ system (including sensor overlay and monitor display of  
241 their pressure distribution) on their care and comfort. The survey will be administered by the  
242 Research Nurse or the Research Assistant, and will take approximately 10 minutes to complete.

243 In addition, a pressure ulcer risk assessment will be conducted, and demographic information and  
244 information on medical history will be collected from patient charts, to establish a patient profile at  
245 baseline, within 24 hours of admission, by the Research Nurse or the Research Assistant.

246 The Braden Scale will be administered to determine the patient's level of risk at pressure ulceration. The  
247 Braden Scale was developed to assist healthcare providers with assessing a patient's level of risk for  
248 pressure ulcer development and the course of a particular treatment. It is a summated rating scale  
249 composed of six subscales: sensory perception, activity, mobility, moisture, friction, and nutrition. Each  
250 subscale is scored from 1-3 or 1-4, for a total score that ranges from 6-23. A lower total score indicates a  
251 lower level of functioning and therefore a higher level of risk for pressure ulceration. Second, a head-to-  
252 toe skin assessment will be conducted for detection of pressure-related skin changes and for overt  
253 ulceration. It requires circling skin areas where the patient may have skin changes or a pressure ulcer,  
254 and labelling the same area with the numbers 1 to 9, which correspond with stages of skin change and  
255 pressure ulceration as per the staging system developed by the National Pressure Ulcer Advisory Panel  
256 and other skin appearance changes described above. The research nurse will conduct the Braden Scale

Ethics ID number: REB13-0794

Study Title: Effectiveness of a pressure-sensing mattress system for reducing the risk of pressure ulcer formation  
by lowering interface pressure in vulnerable patient populations: Parallel-two-group randomized trial

PI: [name]

Version number/date: V2 01/04/2014

and the head-to-toe skin assessment a second time within 24 hours prior to their discharge date, or on the seventh day (whichever comes first).

The demographic information that will be collected include: sex, date of birth, and race. Information on medical history that will be collected include: Charlston comorbidity index; CBC, pre-albumin and albumin, creatinine, liver function test results (alkaline phosphatase, AST), C reactive protein (CRO), glycosylated hemoglobin, and body mass index (BMI). Patient history data that will be collected include reason(s) for admission/diagnoses, level of bed mobility, bladder management, bowel management, history of cancer and/or treatment, history of cardiovascular disease, history of renal failure, use of immunosuppressive medications, previous pressure ulcers, smoking history, and illicit drug use.

4. Total cost of per admission. This information will be used in determining the cost-effectiveness of the ForeSite PT™ system. This information will be accessed using the participant's personal health number after he or she has been discharged from the hospital.

